### Interim analyses {21b}

This is not applicable.

### Methods for additional analyses (e.g., subgroup analyses) {20b}

This is not applicable.

### Methods in analysis to handle protocol non-adherence and any statistical methods to handle missing data {20c}

This is not applicable.

### Plans to give access to the full protocol, participant-level data, and statistical code {31c}

Information from the full protocol will be published in a peer-reviewed journal. The relevant data analyzed during the development of this study protocol are available upon request from the corresponding author.

## Oversight and monitoring

A team from Tehran University of Medical Sciences and a peer reviewer (audit) from Iran National Science Foundation (INSF) will regularly monitor the study implementation and datasets and make recommendations on necessary protocol modifications or termination of all or part of the study.

### Composition of the coordinating center and trial steering committee {5d}

This is not applicable.

### Composition of the data monitoring committee, its role and reporting structure {21a}

Data monitoring will be coordinated by INSF. The auditors will follow a monitoring plan to verify that the clinical trial is conducted and that data are generated, documented, and reported in compliance with the protocol and the applicable regulatory requirements.

### Adverse event reporting and harms {22}

Due to the nature of the intervention, there is no adverse event and no harm in this study. Based on our knowledge, the study will not have any negative consequences.

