**Methods:**

A four-armed, parallel-design randomized controlled trial will be conducted on pregnant women. One hundred and twenty women will be randomly assigned to four groups including three intervention groups and one control group. The intervention groups included the following: (1) motivational interviewing; (2) face-to-face information, motivation, and behavioral skills model; and (3) information, motivation, and behavioral skills model provided using a mobile application. The inclusion criteria include being literate, being in gestational age from 24 to 32 weeks, being able to speak Persian, having no complications in the current pregnancy, having no indications for Cesarean section, and having enough time to participate in the intervention. The primary outcome of the study is the mode of delivery. The secondary outcomes are women’s intention to undergo Cesarean section and women’s self-efficacy.

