**Discussion:**

The interventions of this protocol have been programmed to reduce unnecessary Cesarean sections. Findings may contribute to a rise in normal vaginal delivery, and the effective intervention may be extended for use in national Cesarean section plans.

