## Introduction

### Background and rationale {6a}

Cesarean section (CS) is an important surgical procedure, when normal vaginal delivery (NVD) imposes a risk to mother and/or baby [1]. The World Health Organization (WHO) states that a rate of CS between 10 and 15% of all births is ideal; however, the rate is steadily growing in recent years [2]. The average worldwide rate of CS is 18.6%, ranging from 6.0 to 27.2% in the least and more developed countries, respectively. Countries with the highest CS rates are Brazil (55.6%) and Dominican Republic (56.4%) in Latin America and the Caribbean. Iran and Turkey (47.9% and 47.5%, respectively) have the highest rates in Asia [3]. In Iran, the rate is even higher in private hospitals (72–89%) [4–7].

CS can save the lives of mothers and infants in emergency situations. However, current rates suggest that the CS is now used for women with normal and non-complicated pregnancies and births, when it is not medically necessary [8]. Unnecessary CSs could create complications with no benefits to both mother and baby [3, 9–12]. According to an observational study conducted by the WHO in nine Asian countries, women who undergo an unplanned CS before or during labor or who have an assisted (operative) vaginal delivery are more likely to experience morbidity than those who have spontaneous vaginal delivery [13]. As with any surgery, CS is associated with short- and long-term risks that may be minor or severe [14]. CS can be associated with significant short-term risks such as asphyxia, if the uterus is hypoperfused due to anesthesia, scalpel lacerations, and neonatal respiratory morbidities [9]. Other short-term risks of CS include increased risk of infection and lower likelihood of breastfeeding [10, 11, 15]. Moreover, urinary catheterization is associated with post-CS bacteriuria and has been reported to be as high as 11% [16]. Increasing rates of CS are associated with increased maternal and perinatal morbidities [17].

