## Data collection and management

### Plans for assessment and collection of outcomes {18a}

The primary outcome of the intervention (mode of delivery) will be measured using a checklist after the childbirth.

The secondary outcomes will be measured by a questionnaire 1 month after the interventions.

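### The protocol declares in advance that there is no harm, yet lists no maternal or neonatal outcome beyond mode of delivery

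*Protocol article*

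**What the plan says.** Adverse event reporting and harms {22} reads "Due to the nature of the intervention, there is no adverse event and no harm in this study" and adds "Based on our knowledge, the study will not have any negative consequences". It describes no collection of harms.

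The Abstract (Discussion) gives the purpose: "The interventions of this protocol have been programmed to reduce unnecessary Cesarean sections". The Conclusion expects more normal vaginal deliveries as a result.

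Background and rationale {6a} cites an observational study in nine Asian countries, in which "women who undergo an unplanned CS before or during labor or who have an assisted (operative) vaginal delivery are more likely to experience morbidity". The comparison group in that sentence is women with spontaneous vaginal delivery.

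On outcomes, section {18a} says "The primary outcome of the intervention (mode of delivery) will be measured using a checklist after the childbirth", and the Abstract (Methods) says "The secondary outcomes are women’s intention to undergo Cesarean section and women’s self-efficacy". Outcomes {12} lists the same three. The categories of the checklist are not given.

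**The concern.** Section {22} rests its statement on the kind of intervention. Counselling or an app carries little direct risk, but what the counselling is meant to change is how women give birth, and that has consequences for mother and baby. Some women who turn from a requested CS to an attempted vaginal birth will end with an unplanned CS or an assisted delivery. Those are the two routes that the background links to more morbidity than spontaneous birth.

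What is at stake is the final report. A trial that follows this text can state that no harm occurred because it had already said so, not because anyone looked. The Abstract says that an effective intervention may be extended to national CS plans, so readers would take that sentence as evidence.

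There is a related, smaller point. The stated target is unnecessary CS, but the outcome is mode of delivery. A CS that becomes indicated in labour counts the same as one on request unless the two are recorded separately.

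**Working it through.** **1. The sections side by side**

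| Section | Content |
|---|---|
| Harms {22} | No adverse event and no harm, stated before data |
| Abstract, Discussion; Conclusion | Intended effect: fewer CS, more vaginal births |
| Background {6a} | More morbidity after unplanned CS and assisted vaginal delivery than after spontaneous vaginal delivery |
| Outcomes {12}, {18a}; Abstract, Methods | Mode of delivery; intention; self-efficacy |
| Exclusion criteria | Women who develop complications or preterm labour during the study are excluded |

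An attempted vaginal birth can end as spontaneous vaginal birth, assisted vaginal birth or unplanned CS. The background ties two of these three endings to more morbidity than the third. So the intended effect opens a route to possible harm, and the nature of counselling does not close it. No listed outcome measures morbidity. The exclusion rule may also take women with complications out of the data after enrolment.

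The documents do not give the share of attempted vaginal births that end in unplanned CS or assisted delivery, nor morbidity after planned CS. The net effect on health therefore cannot be calculated from them, in either direction.

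**2. How large a shift the design looks for**

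Sample size {14} gives 30 per group and 80% power, but no control rate and no difference, so the figure cannot be reproduced. It can be solved backwards. Inputs: n = 30 per arm; alpha 0.05 from {20a}, taken as two-sided (an assumption); control rates within or at the ends of the 72–89% quoted for private hospitals in {6a}. With p̄ the mean of the two rates,

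power = Φ{ [ |p1 − p2|·√n − 1.96·√(2p̄(1 − p̄)) ] / √(p1(1 − p1) + p2(1 − p2)) }

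Example, 80% to 45.7%: p̄ = 0.6285, so the power is Φ{(0.343 × 5.477 − 1.96 × 0.683) / 0.639} = Φ(0.84) = 0.80.

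| CS rate, control | CS rate detectable with 80% power | Fall |
|---|---|---|
| 72% | 36.6% | 35.4 points |
| 80% | 45.7% | 34.3 points |
| 89% | 57.6% | 31.4 points |

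The trial is powered only for a large move towards vaginal birth, and it plans no measure of what that move does to health.

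**3. What harms data could show if collected**

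Zero events: the one-sided 95% upper limit is 1 − 0.05^(1/n).
- One arm, n = 30: 1 − 0.05^(1/30) = 9.5%.
- Three intervention arms, n = 90: 1 − 0.05^(1/90) = 3.3%.

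Comparison of two arms of 30, same power formula. The event rates are assumptions, since the documents give none.

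| Assumed rates | Expected events (of 30 vs of 30) | Power | Per arm for 80% power |
|---|---|---|---|
| 5% vs 10% | 1.5 vs 3 | 11% | 435 |
| 5% vs 15% | 1.5 vs 4.5 | 25% | 141 |
| 5% vs 20% | 1.5 vs 6 | 42% | 76 |
| 10% vs 20% | 3 vs 6 | 19% | 199 |

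Example, 5% vs 15%: Φ{(0.10 × 5.477 − 1.96 × 0.424) / 0.418} = Φ(−0.68) = 0.25. Pooling the three intervention arms (90 vs 30) leaves this at about 25%. With so few events the normal approximation is rough, but the conclusion does not depend on its precision.

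**The case against.** Four points can be made for the protocol.

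*The checklist may already be detailed.* This stands. Its categories are not shown, and a journal article may leave them to the full protocol. A reader might infer that a shift towards unplanned CS or assisted birth could never be seen. The text does not support that: if the checklist separates these routes, the shift in mode would be visible. The morbidity that follows would still not be among the listed outcomes.

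*The plan measures more than mode of delivery.* This also stands. Intention and self-efficacy are secondary outcomes. They are measured one month after the interventions and are not health outcomes, so the accurate statement is that mode of delivery is the only clinical outcome listed.

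*The background does not show that leaving planned CS is harmful.* Correct. The comparison made is that women "who have an assisted (operative) vaginal delivery are more likely to experience morbidity than those who have spontaneous vaginal delivery", and the same section lists risks of CS itself, such as infection and neonatal respiratory problems. A reader might infer a documented net harm from moving women off planned CS. The documents do not support that; they support a possible harm. A possible harm is enough to make an advance declaration of none untenable.

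*The design already removes most indicated CS.* In part. Women with an indication are not eligible, and those who develop complications are excluded. Indications that arise in labour remain, so the mismatch between unnecessary CS and mode of delivery is reduced but not gone. It calls for a descriptive breakdown, not a new primary outcome.

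A condensed article may leave the details of harms collection elsewhere. The problem here is a positive statement under the harms heading, not a missing detail.

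**Conclusion.** The point holds as a wrong statement in section {22}, together with the lack of any listed health outcome beyond mode of delivery. Followed as written, the plan would report no harm with nothing measured. It does not affect the primary comparison of CS rates and does not show that the interventions are harmful.

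The statistical limit is firm. At 30 per arm, harms data can only be descriptive: about 25% power for an assumed 5% versus 15%, and an upper limit of 9.5% after zero events in an arm. These figures rest on a two-sided 0.05 level, complete follow-up and assumed event rates; every pair of rates tabulated gives power of 42% or less. The change should be made, because the present text invites a safety conclusion that the trial cannot reach with or without the data.

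**What to change.** - Replace the statement in {22} with a plan to tabulate harms descriptively by randomised arm. Count women who develop complications after randomisation in that table, whether or not they stay in the other analyses.
- Make sure the post-birth checklist separates maternal-request CS, medically indicated pre-labour CS, unplanned or intrapartum CS, assisted vaginal birth and spontaneous vaginal birth, and that it records maternal and neonatal complications.
- Keep any CS as the primary outcome. Report maternal-request CS beside it as a descriptive breakdown, because the stated target is unnecessary CS.
- Give counts with confidence intervals, and state that no difference between arms is not evidence of no harm.

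Cost: some extra data entry and one more table. The protocol describes recruitment as already under way, so new fields may be incomplete for women who have already delivered; the number with missing entries should be shown by arm. The sample size does not change, and power to compare harms stays low.

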### Frequency and plans for auditing trial conduct {23}

Every 6 months, we will send a report to the auditor.

### Plans for communicating important protocol amendments to relevant parties (e.g., trial participants, ethical committees) {25}

This is not applicable.

### Dissemination plans {31a}

We will share the results of this study with key stakeholders via presenting in related seminars and publishing in peer-reviewed journals. We will also provide and share monographs with related departments in the Ministry of Health, Iran.

## Discussion

This study aims to assess the effect of IM, IMB, and IMB-App on choosing the mode of delivery in pregnant women. Iran has one of the highest CS rates in the region and the world [60]. In line with increasing unnecessary CS, Iran’s healthcare system was reformed and NVD was on the agenda [19]. Many policy interventions have been performed to reduce unnecessary CS rate [39, 40, 61]; however, they were not sustained for a long time. These experiences indicate that the interventions have not been effective enough. Designing appropriate interventions for promoting NVD and decreasing the use of unnecessary CS is one of the most important WHO recommendations on non-clinical interventions on CS [41].

A large portion of increased unnecessary CS rates in Iran is related to women [26, 31, 34, 35, 62–65]. Several studies have reported women’s important role in increasing CS. Women have some problems when they want to choose the mode of delivery. Several studies have shown that the most common reasons underlying the preference for CS in Iran were deep-rooted fear of labor pain and vaginal birth [26, 34, 66–70], irreversible damage to the body and sexual function [23, 28, 35, 36, 70, 71], safety (mother/ baby) and comfort [20, 28, 33, 34, 63, 72], social convenience of birthing to time (time scheduling) [26, 34, 68–70, 73], religious beliefs [28, 34, 70, 72], and cultural beliefs (having role models; modernity, the capability to do vaginal birth) [20, 63, 72, 74, 75]. We realized that most of the reasons come from their beliefs. Therefore, we need to conduct cognitive intervention to decrease the rate. According to the WHO recommendation, psycho-education interventions may be useful to decrease this trend [41].

Due to the target group and their problems with long-term intervention or attendance at classes, we will use brief intervention. The brief intervention is efficacious in mechanisms of change [76–78]. Among different models and techniques, we supposed MI and IMB models can be an effective method of facilitating behavioral changes in CS. The effectiveness of these models has already been confirmed. There are several examples of successful interventions about this technique in health. Rubak et al.’s review has shown that MI is a scientific setting that effectively helps clients change their behavior [79]. The review has shown that MI can be effective even in brief encounters of only 15 min [79]. Another review indicates the potential strength of the IMB model as a theoretical framework to develop behavioral interventions [80]. In this study, we will use both techniques as our study framework for face-to-face education. In recent years, massive smartphone applications have been used widely and effectively in education [81]. We have created a mobile app based on the IMB model to use in a group of interventions. The content has been designed according to the constructs of IMB model.

### Limitations and strengths

We understand that women may be inclined to respond in certain ways because they come to receive certain services. However, we will ensure that their responses will not affect the service they will receive and ensure confidentiality. The self-report nature of the questionnaire and necessity of owning a smartphone are another limitation.

Diverse interventions will allow the researchers to obtain different perspectives from the outcome. We have designed evidence-based non-clinical interventions to reduce unnecessary CSs targeted at women. Causes of increasing CS rates are various and different between and within countries. Before implementing any intervention on the issue, we should recognize the reasons behind this increase, as well as locally relevant determinants of CS, and the views and cultural norms of women and healthcare providers. Our study is supported by evidence-based (qualitative synthesis and meta-analysis in Iran) (unpublished paper) information. We will also use a mobile app, a technology that is ubiquitous and has no limitations. Another strength is the simple and non-expensive nature of the interventions.

## Conclusion

To the best of our knowledge, this paper is the first published paper that describes the protocol of CS with this design (face-to-face and M-health) in Iran. We believe that our study will lead to decrease unnecessary CS in the health system of Iran, and conducting this intervention can increase NVD. To achieve this goal, a systematic review study is done to assess the reason of CS in Iran.

## Trial status

The recruitment of participants for this study started in December 2019 and is still ongoing. The recruitment is expected to be completed in March 2020.

Current protocol version and date: V2.0, 1 December 2019.

## Abbreviations

CS: Cesarean section
NVD: Normal vaginal delivery
WHO: World Health Organization
TUMS: Tehran University of Medical Sciences
INSF: Iran National Science Foundation
